**Fig. 1 Fig1:**
[figure not shown]
I-change model (De Vries, 2017)

### Computer tailoring technology

Computer-tailoring technology can be defined as the process of adjusting intervention materials to the specific characteristics of an individual through a digitized process [34]. Unlike more static online communication, these interventions provide people with only the information that is relevant to them, as it is often personalized and tailored to the demographic characteristics and specific situations of the participants. As a result, this information is more likely to be considered relevant by the individual and, consequently, to be read [35]. This methodology provides individuals with personalized feedback on risk behaviors through messages adapted to their specific needs of the user while protecting their anonymity [34].

Web-based computer-tailored interventions (WBCT) are cost-effective for a variety of health-related behaviors in the adult and adolescent populations [36–38]. These interventions also have the potential to reach a large proportion of the adolescent population, since in Spain 99,7% of young people are Internet users, with hardly any differences by gender and/or social status [39]. WBTCT interventions improve young people’s accessibility, as they do not have space-time constraints, they generate personalized messages based on the motivational characteristics of participants; can attract the attention of individuals, and improve the processing of transmitted information through multiple senses [40, 41].

As a theoretical and methodological framework, the I-Change model has been applied in other drug use prevention web-based computer tailoring programs in adolescents, with promising results. For example, a randomized controlled trial to prevent alcohol consumption in adolescents, with a theoretical and methodological design similar to that proposed in this article. The intervention successfully reduced binge drinking among 15 and 16-year-olds [40]. In Spain, the cross-cultural adaptation of the intervention designed by Jander et al. has also been carried out with efficacy data for the reduction of alcohol consumption reported [38, 42].

### The study design

The objective of this article is to describe the protocol for the design, the implementation, and the evaluation of a computer-tailored web-based intervention (Alerta Cannabis) aimed to prevent cannabis use among Andalusian adolescents.

## Materials and methods

This project is based on a cluster-randomized controlled trial in which the new program Alerta Cannabis is tested. This section will be divided into three phasesas described in the following figure (Fig. 2). It has been estimated that to carry out this project 36 months are needed.

**Fig. 2 Fig2:**
[figure not shown]
Schedule for the design, implementation, and evaluation of the Alerta cannabis program

### Intervention development

#### Design of the intervention

The intervention will be based on previous studies carried out by the research team [40, 42–44], specifically, it will be based on the Alerta Alcohol program [41]. The development of the content of the intervention will be also based on in-depth interviews with young people in rehabilitation treatment for cannabis use and focus groups with adolescents who are not habitual users of cannabis [45]. A review of the literature will also be carried out to determine the success factors of programs with similar characteristics in cannabis prevention. In addition to being based on scientific evidence, the content of the intervention will be culturally adapted through focus groups with students of similar ages to the target population to learn about the circumstances surrounding cannabis use and the factors associated with cannabis use in Spain (using the I-Change model as a reference). For this qualitative phase, the team follows the COREQ criteria (Consolidated Criteria for Reporting Qualitative research) [46]. Finally, once the content of the intervention is developed, a focus group will be held with experts in prevention to validate it. An advisory and research team will also be consulted in the development of an online intervention for web content development. To finish this stage, a pilot study of the web intervention will be carried out with different class groups to confirm its feasibility and acceptance by the students (feasibility test) [47].

#### Intervention characteristics

This program will be implemented during the academic year during school hours. It is intended for adolescents between the ages of 14 and 18. It consists of four half-hour sessions given once a week or every two weeks by the professors, except for the first, where, in addition to the professors, a member of the research team will be present face-to-face or online, to explain what the course consists of program and how to use the application. Teachers will previously receive all the information about the program through the school counselor, they will even be able to register and use the platform if they want to explore it beforehand. The program is designed to be self-administered, individualized, and personalized, and is very intuitive. The Alerta Cannabis intervention will consist of preventive messages and personalized information on the benefits of not using cannabis, based on the I-Change model. In the first intervention session, the knowledge and risk of cannabis use will be addressed (level of danger, susceptibility, and severity), as well as the pros of cannabis use. In the second session, the cons of cannabis use (emphasizing the negative aspects of its consumption to foster an attitude of rejection of it) and the social model will be worked on (helping adolescents to choose the models they consider most appropriate and encouraging them to seek the support of friends and family who do not use cannabis). In the third session, social norms (helping adolescents to deal with the perceived approval of cannabis use in their environment as well as to choose real relationships that can help them avoid their use) and social pressure (avoiding the influence of people who consume cannabis in their environment) will be worked on. The fourth session is a reinforcement session in which all the aforementioned concepts are worked on and, in addition, the challenge of not consuming cannabis will be proposed to the participants. To evaluate the challenge, the participants who accept it will receive an e-mail asking them to answer whether or not they have been able to overcome the challenge. In all sessions, skills (self-efficacy and action plans) will also be worked on to reject cannabis.

Before starting the first session of the intervention, participants will have to complete an initial questionnaire (pre-test) and two follow-up questionnaires (post-test at six months and twelve months).

### Implementation phase

#### Study design

A two-arm cluster-randomized controlled trial (CRCT) will be designed, with an experimental condition (EC) and a control condition (CC) condition will be randomized at the school level. An initial assessment (pretest) and two assessments (post-test) will be performed at six and twelve months. The allocation ratio will be 1:1 using an online randomization system [48] (Fig. 3). Randomization will be performed by a member of the research team. Randomization will be carried out in batches, since after previous studies we have verified that not all schools confirm their participation in the program within the stipulated period, delaying the start of the rest of the schools in the program. Two school recruitment periods will be stipulated to reach the desired sample size within the same academic year. Participants will be blinded, only knowing that they will be participating in a cannabis prevention project.

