**Methods:**

The Alerta Cannabis research project consists of design, implementation, and evaluation. In the first phase, a computer-tailored eHealth program (Alerta Cannabis) is developed based on the I-Change Model, an integrated model based on three main behavioral change processes: awareness, motivation, and action. This program consists of four 30-minute sessions that will provide culturally adapted and personalized advice to motivate students not to use cannabis through text feedback, animations, and gamification techniques. This phase will also include usability testing. In the implementation phase, secondary school students from Western Andalusia, Spain (Seville, Cádiz, Huelva, and Córdoba) and Eastern Andalusia (Jaén, Málaga, and Granada) will be randomized to an experimental condition (EC) or a control condition (CC) for a cluster randomized clinical trial (CRCT). Each condition will have 35 classes within 8 schools. GI will receive the online intervention Alerta Cannabis. EC and CC will have to fill out a questionnaire at baseline, six months, and twelve months of follow-up. In the last phase, the effect of Alerta Cannabis is evaluated. The primary outcomes are the lifetime prevalence of cannabis use and its use in the last 30 days and at 6 months. At 12 months of follow-up, the prevalence in the last 12 months will also be assessed. The secondary outcome is the intention to use cannabis.

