#### Selection and collection of samples

Contact will be made with all Andalusia schools that have students between the aged of 14 and 18 in their classrooms. According to the data provided by the Education Webpage of the Junta de Andalucía [50] (using the filters secondary education, intermediate vocational training, basic vocational education, and baccalaureate) 119 provincial capital schools can be approached. A member of the investigative team will call all schools. All information provided by telephone will also be mailed to schools interested in participating (program manual, manual summary, application management document, resolution of the Ethics Committee, active consent for parent’s form). This parent-consent form must be signed by parents through iPasen [51], which is the mobile application of the Department of Education and Sports of the Junta de Andalucía that allows communication between different members of the educational community (legal guardians, students, management positions and teachers). Some school nurses also assisted in recruiting schools, during the second batch of recruitment.

Weekly, members of the team will call the counselors of these centers to obtain their definitive participation. The randomization process will be carried out using the Research Randomizer computer software (Version 4.0) [48]. Over the phone, agreements will be made on the dates for the sessions. During the first session, a member of the research team will be present face-to-face or online, so that the teacher who will be present with the students in the next session knows how the platform works (although previously the teacher has been able to use the platform to find out how does it work).

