## Evaluation phase

### Effectiveness and process evaluation

General descriptive statistics will be used to describe the baseline characteristics of the participants. Since the students will be nested within a class in the study and classes will be nested within schools, to examine the predictors of dropout versus non-dropout, a multilevel logistic regression analysis will be conducted. In addition, a multilevel approach will be used to assess the effects of the intervention on the behavior of cannabis use. The first level will be repeated measures within the participants (baseline and two follow-up measurements), the second level will be the student, the third level is the class, and the fourth level is the school.

Baseline cannabis will use behavior and the demographic variables described above will be included as covariates. To select significant predictors and interactions, a backward deletion procedure (a = 0.05) will be used, with the restriction that predictors will not be removed from the model if they were involved as terms.

To study the predictors of adherence, we will also analyze the associations between the potential characteristics (i.e., gender, age, academic course, religion, nationality, family wealth score, Apgar score, and cannabis use at baseline) on the one hand, and participation in the intervention (i.e., adherent or not) through the number of sessions attended by participants at schools on the other.

Finally, for the process evaluation, a descriptive analysis will be performed using chi-square tests to examine differences between males and females and between cannabis users and non-users. We use SPSS Statistics for Windows, version 26.0 (IBM Corp.), for these analyses.

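### Schools are randomised in batches, but the stated effect model has no batch term: a loss of precision if batches differ, and possible chance imbalance if 1:1 is not held within batch

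*Protocol article*

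**What the plan says.** All places are in the protocol article.

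- **Study design** (Implementation phase): the two conditions "will be randomized at the school level". "The allocation ratio will be 1:1 using an online randomization system". "Randomization will be carried out in batches, since after previous studies we have verified that not all schools confirm their participation" by the deadline, which would hold up the other schools. "Two school recruitment periods will be stipulated to reach the desired sample size within the same academic year". The section does not say whether the 1:1 ratio is held inside each batch.
- **Selection and collection of samples**: "Some school nurses also assisted in recruiting schools, during the second batch of recruitment".
- **Abstract, Methods**: "Each condition will have 35 classes within 8 schools", so 16 schools in all.
- **Effectiveness and process evaluation**: a multilevel model with four levels (measurement occasion, student, class, school) and none for batch. On adjustment, the article says: "Baseline cannabis will use behavior and the demographic variables described above will be included as covariates". Predictors and interactions are then selected by backward deletion at 0.05. The one stated restriction on removal does not mention batch.

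**The concern.** When schools are allocated batch by batch, batch is part of the randomisation structure. Good practice is to carry that structure into the analysis, especially with few randomised units.

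Batch may also be related to outcome. The second batch consists of schools that confirmed later, and some were recruited with nurses' help. If it also starts later, its assessments fall at a different point in the year, and past-30-day use could respond to that. Baseline adjustment need not remove such a difference, because baseline would be measured at a different time as well. This is inference: the article gives neither start dates by batch nor any batch effect.

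Two consequences are possible:

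- If allocation is balanced within batch, leaving batch out moves the batch difference into the school-level variance, and the test becomes conservative.
- If allocation is not balanced within batch, one arm can by chance hold most of one batch, and the unadjusted effect then carries part of the batch difference.

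The deletion rule adds to this. A batch term added later would be open to removal for non-significance unless it is exempted.

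**Working it through.** **Plan figures.** The article gives no batch effect, so there is no plan figure to reproduce on this point. Its 87% power statement does not bear on it. That figure is a separate matter: the stated inputs give a design effect of 1 + 24 × 0.2 = 5.8, an effective 1500/5.8 = 258.6 per arm, and 93.4% two-sided power for 50% against 35%.

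**Inputs.** From the article: 16 schools, 8 per arm, two recruitment periods (taken here as two batches), no batch term. Assumed: batch sizes 8/8, 10/6 or 12/4; SD of school means within batch = 1 (this covers all variance of a school mean, including class and student variation); batch shift of 0 to 1.5 SD; true effect 1.5 SD; t-test on school means at two-sided 0.05; 6000 simulated trials per setting (Monte Carlo error on power about 0.005 to 0.006).

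**Step 1: no batch shift, balanced within batch.** SE = √(1/8 + 1/8) = 0.5, so the non-centrality is 1.5/0.5 = 3. Power is 0.80 on 14 df and 0.79 on 13 df. The term costs about 1 point.

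**Step 2: batch shift present.**

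| Shift (school SD) | 1:1 within batch: power without / with term | Schools allocated independently: power without / with term |
|---|---|---|
| 0 | 0.80 / 0.79 | 0.76-0.78 / 0.72-0.74 |
| 0.5 | 0.77-0.79 / 0.79-0.80 | 0.74-0.75 / 0.73-0.74 |
| 1.0 | 0.72-0.74 / 0.79-0.80 | 0.66-0.68 / 0.72-0.73 |
| 1.5 | 0.60-0.64 / 0.78-0.80 | 0.56-0.62 / 0.72-0.74 |

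With 1:1 within batch, type I error without the term is about 0.03 at 1 SD and 0.014-0.018 at 1.5 SD. The effect estimate is the same with or without the term. With independent allocation, type I error stays near 0.05 either way.

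The independent-allocation column lets arm sizes vary, whereas the article gives 8 per arm. The cost of the term at no shift can be computed for fixed 8:8 arms and 8/8 batches. With k experimental schools in batch 1, the arm-batch correlation is r = (k − 4)/4, the adjusted SE is 0.5/√(1 − r²), and k has probability C(8,k)²/12870. Averaging power on 13 df over k gives 0.76, against 0.80 unadjusted. The cost is again about 4 points.

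**Step 3: translation to SE.** For equal batches, a shift d explains R² = (d²/4)/(1 + d²/4) of the total variance of school means, so d = 1 gives 0.25/1.25 = 0.20. Omitting batch inflates the SE by about 1/√(1 − R²): 1.05, 1.12 and 1.20 at R² = 0.1, 0.2 and 0.3. The 5-20% range rests on those assumed values, and R² must be batch's share of the total variance of school means. If batch explained 10-30% of the between-school component only, and that component were half the total (assumed), R² would be 0.05-0.15 and the inflation about 3-8%.

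**Step 4: chance imbalance.** With 8/8 batches, 8/8 arms and no restriction within batch, a 6-2 or worse split of a batch has probability 2 × (28² + 8² + 1²)/12870 = 1698/12870 = 13.2%. In a 6-2 split, 6/8 of one arm and 2/8 of the other come from batch 1. The unadjusted effect then carries 6/8 − 2/8 = one half of the batch difference.

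**The case against.** The strongest reply is that this is a condensed article, and that stratum handling could sit in a full protocol or analysis plan that is not shown. The covariate list is not declared exhaustive. That limits the weight of the point but does not remove it: the article does state the model, the covariates and the selection rule, and batch is absent from all three.

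The evidence that batches differ is thin. It amounts to one sentence about some nurses assisting, both recruitment periods fall in one academic year, and the follow-up times are the same. Baseline use, already a covariate, would absorb much of any stable difference. This stands, and it is why the size is conditional on an assumed shift.

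A reader might infer that batch is confounded with condition. The article does not support this. Systematic confounding needs allocation probabilities that differ by batch, for example a second batch used to fill up one arm, and nothing says so. An odd-sized or unevenly split batch gives only chance correlation, which is unbiased over randomisations. A reader might also fear unequal arms overall, but the abstract gives 8 schools per condition; only the split within batches is open.

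Nor is the term free: where allocation is not balanced by batch and batches do not differ, it loses about 4 points of power.

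**Conclusion.** The point holds as one of precision and chance imbalance, not of validity. The school random effect takes up unmodelled batch variance, so the planned test does not become anti-conservative.

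Under 1:1 allocation within batch, retaining batch gains roughly 6 to 7 power points at an assumed shift of 1 school SD, 1 to 2 points or less at 0.5 SD, and loses about 1 point at none. Without balance within batch, the risk is a chance split that carries part of a batch difference into the unadjusted effect. The power figures rest on an assumed effect of 1.5 school SD, assumed batch sizes and a school-means approximation to the four-level model. They show direction and rough size and do not forecast this trial. The finding is modest and cheap to act on.

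**What to change.** 1. State whether the 1:1 ratio is held within each batch. If allocation is still to be done, restrict it so that it is. If it is done, report the number of schools per condition by batch.
2. Include batch as a fixed effect in the primary and secondary effect models, and exempt it from backward deletion.

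Cost: recording the batch of each school, and one of the 14 school-level degrees of freedom. If batches turn out not to differ, the power loss is about 1 point with allocation balanced within batch and about 4 points without, so the two parts belong together.

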**Fig. 3 Fig3:**
[figure not shown]
The flow diagram of the intervention describes the steps followed to carry out the intervention, as well as the two study conditions. Sessions for each condition will be also described. The sessions are held at the school and a teacher is present

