#### Control condition

Participants in the control condition only will complete one initial questionnaire (pre-test) and two follow-ups (post-test) at six and twelve months.

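### The protocol declares participants blinded, but students cannot be blind to a four-session programme compared with questionnaires only, and all cannabis outcomes are self-reported

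*Protocol article*

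**What the plan says.** Protocol article, Implementation phase, Study design: "Participants will be blinded, only knowing that they will be participating in a cannabis prevention project". Schools are the unit of randomisation.

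Intervention characteristics, on the experimental programme: "It consists of four half-hour sessions given once a week or every two weeks by the professors". The second session works on the drawbacks of cannabis, "emphasizing the negative aspects of its consumption to foster an attitude of rejection of it". In the fourth, "the challenge of not consuming cannabis will be proposed to the participants", and "the participants who accept it will receive an e-mail asking them to answer whether or not they have been able to overcome the challenge".

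Control condition: "Participants in the control condition only will complete one initial questionnaire (pre-test) and two follow-ups (post-test) at six and twelve months". No sham or attention programme is described.

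Abstract, Methods: "The primary outcomes are the lifetime prevalence of cannabis use and its use in the last 30 days and at 6 months"; 12-month use is added at the last follow-up, and intention is secondary. The Measurements section takes all of these from survey questions answered by the student. No objective verification is stated.

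The limitations in the Discussion cover exposure to other prevention programmes and unmeasured confounders. They do not mention reporting bias.

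**The concern.** Blinding of participants means that they do not know which intervention they received. Here one arm sits through four sessions openly directed against cannabis and the other fills in forms. Students who know that the project concerns cannabis prevention can see whether they were given any. The sentence therefore claims a property that the design cannot have.

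That a behavioural programme cannot be blinded is normal and is not the complaint. It matters here because the outcomes are unverified self-reports of illegal drug use. The programme encourages rejection of cannabis and asks students to take on a challenge not to use it, and controls get nothing comparable. Some experimental users may become less willing to admit use without having changed their behaviour, and that would look like benefit. A larger sample does not remove such a bias. Nor does the multilevel model with baseline use as a covariate, because the extra denial would arise after baseline and in one arm only. A later report that repeated the blinding statement would give readers assurance they should not have.

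**Working it through.** **Blinding claim against design (no arithmetic needed)**

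| Feature | Experimental | Control |
|---|---|---|
| Told that the project is about cannabis prevention | yes | yes |
| Anti-cannabis sessions | four | none |
| Challenge not to use cannabis | offered in session 4 | none |
| E-mail about the challenge | those who accept | none |
| Cannabis outcomes | self-report | self-report |

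Rows 2 to 4 are visible to the student. Because whole schools are randomised, students may not know that another condition exists. That is the most the blinding sentence can mean. Teachers receive information about the programme beforehand and give the sessions, so they are not blind to it either.

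**Illustrative size**

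The plan gives no misreporting figure, so there is nothing of its own to reproduce.

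Inputs:
- Lifetime prevalence p = 21.4% (Introduction, Andalusia, ages 14 to 18).
- For range, p = 28.6% (Introduction, Spain, same ages; recall period not stated there).
- 875 students per arm, intracluster correlation 0.2, clusters of 25 (Sample size).
- Fraction u of users who deny use in the experimental arm only. **This is an assumption**; 5%, 10% and 20% are shown.

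With no true effect, the control arm reports p and the experimental arm reports p(1 − u). The spurious difference is p × u and the apparent risk ratio is 1 − u.

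| u | p = 21.4% | p = 28.6% | Risk ratio |
|---|---|---|---|
| 5% | 1.1 points | 1.4 points | 0.95 |
| 10% | 2.1 points | 2.9 points | 0.90 |
| 20% | 4.3 points | 5.7 points | 0.80 |

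At 21.4% there are 875 × 0.214 ≈ 187 ever-users per arm, so u = 10–20% means about 19 to 37 students changing their answer.

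**Chance of a false significant benefit in lifetime use**, by a simple two-proportion comparison at two-sided 5%:
- Design effect = 1 + (25 − 1) × 0.2 = 5.8, so the effective n per arm = 875 / 5.8 ≈ 151.
- Chance = Φ[(p·u − 1.96·SE₀) / SE₁], with SE₀ pooled and SE₁ unpooled.
- u = 10%: (0.0214 − 1.96 × 0.0463) / 0.0463 ≈ −1.50, giving about 7%.
- u = 20%: (0.0428 − 1.96 × 0.0454) / 0.0453 ≈ −1.02, giving about 15%.
- The nominal chance in that direction is 2.5%.

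These are approximations. The planned analysis is a four-level model, and randomisation is by school, whereas the sizing uses clusters of 25.

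**The case against.** The strongest reply is that the sentence states its own scope: students know only that they are in a prevention project. With whole schools randomised, it can be read as saying that students are not told of the comparison. That information is useful and should be kept. But the word used is blinded, and the sentence does not limit it to that meaning.

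Several stronger readings are tempting, and the documents do not support them.

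- *The protocol relies on blinding to prevent reporting bias.* No section links the two.
- *Supervision by a teacher differs between arms.* The Fig. 3 legend introduces the sessions of both conditions and then says "The sessions are held at the school and a teacher is present". As written, that covers both arms. The programme is also described as self-administered.
- *The whole experimental arm pledges abstinence and is e-mailed.* The challenge is proposed, and only those who accept are contacted. Nothing says that their replies are linked to the outcome questionnaire. The Computer tailoring technology section refers to anonymity, and the ethics section to confidentiality and an approved data management protocol. These are general assurances and do not equalise pressure between arms.
- *Differential denial could account for the planned effect.* The planned 10% reduction concerns 30-day use, whereas 21.4% is lifetime prevalence. Dividing 10 points by 21.4% to get a required denial rate of 47% mixes two outcomes. Saying that 10% denial reproduces a 10% relative reduction is an identity and not evidence.

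It is also fair to say that the denial rate is assumed, and that at the plan's own intracluster correlation the chance of a false positive rises only to about 7–15%. Detailed administration procedures, such as scripts, form design and screen visibility, are matters that an article may leave to the full protocol, so their absence is not criticised here.

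**Conclusion.** The blinding statement is wrong as written. Students cannot be blind to the programme; at most they are unaware of the comparison. Because the use outcomes and intention are all self-reported, differential under-reporting in favour of the experimental arm is possible. It is not shown to occur, and its size cannot be derived from the documents.

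The only size that can be given is conditional. With no true effect, 21.4% lifetime prevalence and an assumed 10–20% of ever-users denying use in the experimental arm only, the spurious difference in lifetime use is 2.1–4.3 points. Without an Andalusian 30-day prevalence, this does not carry over directly to the outcome used for sizing. In the same population 30-day prevalence cannot exceed lifetime prevalence, so at an equal denial rate the difference there would be no larger.

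This should be corrected. The reason is the inaccurate statement and the low cost of a check, not evidence of a large bias.

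**What to change.** 1. Reword the sentence in Study design, for example: *Students are not told of the comparison, but students and teachers are not blinded to the programme; outcomes are self-reported.* Name differential reporting as a limitation in the Discussion.

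2. State that replies to the challenge e-mail are kept out of the outcome data.

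3. Pre-specify one check. Among students who report lifetime use at baseline, compare by arm the proportion who later report never having used. Report it beside the primary result, with a sensitivity analysis that counts those students as ever-users in both arms. The lifetime item and the repeated measures within students are already planned, so no new data are needed.

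The check has limits that should be stated with it. A higher retraction rate in the experimental arm would suggest differential denial but not prove it, because careless or exaggerated baseline answers that are later corrected give the same pattern. It covers lifetime use only, and it cannot detect denial by students who start after baseline, an important group in a prevention trial.

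The cost is wording, one extra descriptive analysis with its sensitivity analysis, and a less favourable blinding statement.
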